## Abstract

**Background:**

Systematic reviews and meta-analyses based on observational studies have shown voluntary medical male circumcision (VMMC) may reduce HIV risk among men who have sex with men (MSM). There is a lack of randomized controlled trial (RCT) data assessing the efficacy of VMMC.

**Objective:**

The primary objective of this study is to assess the efficacy of VMMC for preventing HIV acquisition among MSM who primarily engage in insertive anal sex.

**Methods:**

A multicenter RCT will be conducted among MSM in 8 cities in China. Eligible participants are men aged 18-49 years who self-report ≥2 male sex partners in the past 6 months, predominantly practice insertive anal sex, and are willing to undergo circumcision. Interested men who satisfy inclusion criteria will be tested for HIV 1 month before enrollment and at enrollment, and only those who are HIV negative will be enrolled. At baseline, all enrolled participants will be asked to report sociodemographic characteristics and sexual behaviors; provide a blood sample for HIV, syphilis, and herpes simplex virus type 2 testing; and provide a penile swab for human papillomavirus testing. Participants will be randomly assigned to the intervention or control group. Those in the intervention group will receive VMMC and undergo a web-based weekly follow-up assessment of postsurgery healing for 6 consecutive weeks. All participants will be tested for HIV at 3-, 6-, 9-, and 12-month follow-ups. All participants will also be asked to report sexual behaviors and undergo repeat herpes simplex virus type 2 and human papillomavirus testing at 6- and 12-month follow-ups. The primary end point is HIV seroconversion. Secondary end points are the safety and satisfaction with VMMC and the changes in sexual behaviors after VMMC. The grouped censored data will be analyzed by intention-to-treat approach.

**Results:**

Recruitment for the RCT began in August 2020 and continued through July 2022. Data collection is expected to be completed by July 2023, and full data analysis is going to be completed by September 2023.

**Conclusions:**

This study will be the first RCT to assess the efficacy of VMMC in preventing HIV infection among MSM. Results from this trial will provide preliminary evidence for the potential efficacy of VMMC to reduce incident HIV infection among MSM.

**Trial Registration:**

Chinese Clinical Trial Registry ChiCTR2000039436; https://www.chictr.org.cn/showproj.html?proj=63369

**International Registered Report Identifier (IRRID):**

DERR1-10.2196/47160

## Introduction

### Overview

Men who have sex with men (MSM) are at high risk for HIV infection. Evidence-based HIV preventive measures for MSM include behavioral interventions (eg, condom use) and biomedical interventions (eg, preexposure prophylaxis [PrEP] and postexposure prophylaxis [PEP]). Condoms are highly effective in preventing HIV transmission, but the prevalence of condomless sex remains high among MSM [1,2]. HIV PrEP reduces risk of HIV infection, but uptake among MSM is limited [3]. The effectiveness of HIV PEP is constrained by lack of awareness, limited availability of PEP services, and poor adherence to medications and clinic follow-ups, particularly in resource-limited settings [4-6]. Innovative, effective, and acceptable HIV prevention measures are needed to complement and expand existing prevention strategies among MSM.

Voluntary medical male circumcision (VMMC) may protect men from HIV infection by reducing mucosal surface area and the concentration of HIV target cells in the penis [7,8]. Three large randomized controlled trials (RCTs) in Africa found that VMMC reduced the risk of HIV infection by 50%-60% among heterosexual men [9-11]. Debate remains on whether VMMC can effectively prevent HIV acquisition among MSM. Two systematic reviews and meta-analyses in 2008 and 2011 [12,13] showed that there was no statistically significant association between VMMC and HIV acquisition among MSM. However, new evidence has emerged over the past 10 years. A 2018 meta-analysis found that VMMC may reduce risk of HIV infection by 20% among MSM [14]. Similarly, a 2019 systematic review and meta-analysis of 67 observational studies [15] reported that VMMC was associated with a 23% lower odds of HIV infection among MSM overall and 42% lower odds of HIV among MSM in low- and middle-income countries. Furthermore, VMMC was associated with a 16% lower odds of herpes simplex virus and a 29% lower odds of penile human papillomavirus (HPV) infection among MSM living with HIV [15]. Another systematic review in 2019 [16] found VMMC was associated with 7% and 38% lower odds of HIV infection among MSM overall and MSM in Asia and Africa, respectively. These systematic reviews found that no previous RCTs have evaluated the impact of circumcision on HIV acquisition among MSM. Interventional trials are needed to confirm the findings of previous observational studies.

Sexual position preference may have a significant impact on the efficacy of VMMC to reduce HIV infection among MSM. Men who practice insertive anal sex may benefit more from VMMC than those who practice receptive anal sex. Subanalysis in a 2019 systematic review and meta-analysis [15] found that MSM who primarily engage in insertive anal sex had a 56% lower odds of HIV infection, a stronger association compared to what was found among MSM overall. In China, 70% of MSM practice either exclusively insertive anal sex or both insertive and receptive anal sex [17,18]. Thus, VMMC has the potential to become an important HIV prevention option for most MSM in China.

Only 15.3% of MSM in China have undergone circumcision [19]. This proportion is lower than the global average of 37%-39% [20]. Mainstream social conventions and religious practice in China are neutral on circumcision, neither promoting nor forbidding the procedure. Implementing a VMMC intervention in China should not be significantly hindered by Chinese traditions or cultural values. Other potentially effective interventions, such as PrEP, are still in promotion phase in China, which is impeded by high cost, low accessibility, and stigma among MSM [21,22]. As for consistent condom use, the rate of its use among MSM remains relatively low, approximately 50% [23,24]. Hence, it is essential to determine an alternative HIV prevention strategy in China. Given the high proportion of Chinese MSM who are uncircumcised and the need for alternative HIV prevention strategies in China, it is theoretically feasible to conduct an RCT to evaluate the efficacy of VMMC to reduce incident HIV infection among MSM in China. This RCT could provide valuable information to inform HIV prevention policy as well as future mathematical models and additional clinical trials of VMMC.

### Objectives

The primary objective of this study is to assess the efficacy of VMMC for preventing HIV acquisition among MSM who primarily engage in insertive anal sex. The secondary objectives are to assess (1) the safety of and satisfaction with surgical VMMC among MSM; (2) changes in reported sexual risk behaviors after circumcision among MSM; and (3) the efficacy of VMMC for preventing sexually transmitted infections (STIs), including herpes simplex virus type 2 (HSV-2), syphilis, and penile HPV among MSM. Our hypothesis is that VMMC could reduce the risk of HIV infection among MSM.

## Methods

### Study Design

This is a multicenter RCT to evaluate the efficacy of VMMC on incident HIV infection among MSM in China over a 12-month follow-up period (Figure 1).

**Figure 1 figure1:**
[figure not shown]
The flow chat of the CoM (circumcision of men who have sex with men) Study. RCT: randomized controlled trial.

### Study Setting

The VMMC and incident HIV infection among MSM in China (circumcision of men who have sex with men [CoM] Study) will be conducted in 8 cities in Mainland China: Beijing, Tianjin, Qingdao, Chongqing, Shenzhen, Guangzhou, Foshan, and Luzhou (Table 1).

This study began on August 1, 2020, and is scheduled to be completed by September 31, 2023. The study has 3 phases: eligibility screening, enrollment, and follow-up (Table 2).

**Table 1 table1:** Study sites of the CoM (circumcision of men who have sex with men) Study.

City and province	Study site	Nature of study site
Beijing	Beijing You’an Hospital, Capital Medical University	Tertiary hospital
Tianjin	Tianjin Centers for Disease Control and Prevention	Provincial CDC^a^
Qingdao, Shangdong	Qingtong Volunteer Service Center for HIV/AIDS Prevention	NGO^b^
Guangzhou, Guangdong	Guangzhou Zhitong Public Service Center	NGO
Shenzhen, Guangdong	Shenzhen Rainbow 258 Center for Men	NGO
Foshan, Guangdong	Foshan Pengyou Care and Rescue Center for AIDS Prevention	NGO
Chongqing	AIDS/STD^c^ Control and Prevention Institute, Chongqing CDC	Provincial CDC
Luzhou, Sichuan	Luzhou Red Ribbon Heart Association	NGO

^a^CDC: centers for disease control and prevention.

^b^NGO: nongovernmental organization.

^c^STD: sexually transmitted disease.

**Table 2 table2:** Schedule of events of the CoM (circumcision of men who have sex with men) study.

Events		Eligibility screening	Enrollment	Follow-up			
		Month 1	Month 0 (baseline)	Month 3	Month 6	Month 9	Month 12
**Recruitment and enrollment**							
	Screening questionnaire	**√**					
	One-on-one consultation	**√**					
	Watching enrollment videos	**√**					
	Informed consent		**√**				
	Assignment of study group		**√**				
	Intervention^a^		**√**				
**Assessments**							
	HIV rapid testing	**√**	**√**	**√**	**√**	**√**	**√**
	Baseline questionnaire		**√**				
	Follow-up questionnaire				**√**		**√**
	STIs screening^b^		**√**		**√**		**√**

^a^For participants in the intervention group, they will be formally enrolled after completing the circumcision. There is a maximum waiting period of 3 months for surgery and a 6-week postoperative recovery period before formal follow-up phase. For participants in the control group, they will remain uncircumcised at enrollment and follow-up, and they will enter the formal follow-up phase after completing the enrollment and baseline questionnaire.

^b^STIs include herpes simplex virus type 2, syphilis, and penile human papillomavirus.

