### Interventions

VMMC is the intervention to be evaluated in this study. Men in the intervention group will undergo VMMC within 3 months of randomization, and they could choose one of 2 types of circumcision (disposable circumcision stapler surgery and conventional surgical procedure), while those in the control group will remain uncircumcised during the follow-up. All men will be followed for 12 months.

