### Participant Recruitment and Enrollment

As the distribution of our target population unknown and MSM in China are a hard-to-reach population, we will use convenience sampling and snowball sampling to recruit participants. A public account on WeChat (a multi-purpose instant messaging app developed by Tencent, with over 1 billion active monthly users) will be used to communicate with participants. Recruitment, enrollment, provision of health education, and participant follow-up will be accomplished through WeChat. This RCT will also recruit and enroll potential participants in collaboration with local MSM community–based organizations by using their organizational WeChat accounts and in-person outreach activities. An offline survey will be carried out at MSM community–based organizations and the department of dermatology at participating hospitals.

A QR code which links to an online screening questionnaire will be included in recruitment materials. Recruitment materials will include paper materials (eg, posters, folding pages, table tent cards, and business cards) and video materials (ie, a 2-minute enrollment video with a brief introduction and a 15-minute enrollment video with detailed information). Paper and video materials will include summaries of the following: (1) current state of research on efficacy of VMMC to prevent HIV infection; (2) potential benefits of VMMC; and (3) potential risks of VMMC. Potential participants will be invited to scan the QR code included in these paper or video materials and then complete a web-based screening questionnaire with preprogramed logic to assess eligibility.

Eligible men will be invited to participate in this study. Men who agree to participate will receive a face-to-face introduction to the CoM Study by a trained investigator at the study site. Questions about the study will be answered by these investigators during these introductions. For men who are willing to undergo VMMC, HIV rapid testing will be conducted 1 month before enrollment and at enrollment.

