### Randomization and Follow-Up

Eligible men will be randomized using a 1:1 allocation ratio to the intervention and control groups. Randomization lists for each study site have been pregenerated by researchers. Each envelope with a unique number will be assigned for 1 allocation sequence, into which a card with grouping information will be put before sealing. Trained investigators at each study site will assign an envelope to each participant according to the order of the participant’s arrival. Participants cannot be blinded due to the nature of the intervention. After randomization, trained researchers will provide HIV prevention counseling to participants in both groups, including promotion of consistent condom use and regular HIV testing.

Participants randomized to the intervention group will be encouraged to complete VMMC within 1 week of enrollment. Time to VMMC can be extended up to 3 months after enrollment on a case-by-case basis. We recommend participants to undergo VMMC at a secondary or higher-level medical center of their own choice. Although the clinical VMMC activities are not part of study procedures, a research assistant would accompany the participants to the hospital to undergo the circumcision. This trial will provide a surgical subsidy of CNY 1000 (US $160). If participants do not complete VMMC within 1 month of enrollment, a text message reminder will be sent. The surgeon will check the condition of the foreskin of participants before the operation to determine if surgery is necessary. Men in the intervention group will be advised to abstain from sex for 6 weeks after undergoing VMMC, and the 12-month follow-up period will begin after this 6-week period of abstinence. If men resume sexual behaviors earlier than 6 weeks after VMMC, then the 12-month follow-up period will begin at the time of their first sexual encounter after VMMC.

Men randomized to the control group will complete the baseline survey after enrollment. The 12-month follow-up period for the control group will begin immediately after completing the baseline survey. At the end of the 12-month follow up period, men in the control group will be offered a CNY 1000 (US $160) subsidy to undergo VMMC.

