### Statistical Analysis

All data will be analyzed based on the principle of intention to treat. We will assess the type of missing data and assess attrition effects by testing whether there are systematic differences between dropouts and nondropouts. Key baseline characteristics will be examined between the intervention and control groups to ensure they are balanced; if not, subsequent analyses will assess whether these characteristics are confounding factors of the intervention.

For continuous variables, we will calculate means and SDs, and means will be compared with 2-sample *t* tests or Mann-Whitney tests. For categorical variables, proportions will be compared with chi-square tests or Fisher exact tests. In addition, we assume that HIV status at the end of follow-ups is grouped censored data and suitable for exponential, proportional hazards model with constant baseline hazard. Therefore, differences between the intervention and the control groups will be identified with a Poisson regression model, which includes observed covariates (ie, HIV risk behaviors, such as condom use, number of sexual partners, frequency of insertive anal sex, and HIV-positive sexual partners as well as demographic variables, such as age, education level, and income). Incidence rates will be calculated for each outcome in the 2 groups. Moreover, the incidence rate ratios and their 95% CIs will be estimated using the Poisson regression model. For all the outcome variables, including the primary (ie, HIV incidence) and secondary (ie, penile HPV incidence, clearance and persistent infection, HSV-2 incidence, and syphilis incidence) outcomes of interest, the aforementioned analyses will be repeated across all the visits (ie, 6- and 12-months follow-ups).

The changes in sexual behaviors after VMMC over time between the intervention and the control groups will be compared with the generalized estimating equations. For outcomes of VMMC safety and satisfaction among circumcised MSM, we will perform the same statistical description and comparative analyses described as above.

A 2-sided *P* value lower than .05 will be used to infer statistically significant difference. All the statistical analyses will be performed with R software (version 4.2.1; R Core Team).

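### As written, the VMMC arm cannot be analyzed by intention to treat: enrollment and the follow-up clock both wait for completed surgery, so randomized but unoperated men have no person-time

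*Protocol article*

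**What the plan says.** Group assignment is a Month 0 event in Table 2, and Interventions states: "Men in the intervention group will undergo VMMC within 3 months of randomization". Randomization therefore comes first.

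Footnote a of Table 2 then treats the arms differently. For VMMC men, "they will be formally enrolled after completing the circumcision", and "There is a maximum waiting period of 3 months for surgery and a 6-week postoperative recovery period before formal follow-up phase". For controls, "they will enter the formal follow-up phase after completing the enrollment and baseline questionnaire".

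Randomization and Follow-Up gives the VMMC arm two possible starts for the 12-month clock: the end of the 6-week abstinence that follows surgery, or the first sex after surgery if that is earlier. The control clock starts at the baseline survey. The same section uses enrollment for a point before surgery: "Participants randomized to the intervention group will be encouraged to complete VMMC within 1 week of enrollment". It also provides that "The surgeon will check the condition of the foreskin of participants before the operation to determine if surgery is necessary".

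Interventions promises 12 months of follow-up to all men, and Statistical Analysis states: "All data will be analyzed based on the principle of intention to treat".

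**The concern.** Entry to the VMMC arm depends on an event after randomization, and entry to the control arm does not depend on any comparable event. A man assigned to VMMC may decline, pass the 3-month limit, or be told by the surgeon that surgery is not needed. Under the stated rules he is then never formally enrolled and his follow-up never begins.

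If the rules are followed literally, the primary comparison is operated men against all controls. Men who go through with surgery may differ in HIV risk from men who do not, and randomization would no longer protect the HIV result. Few events are expected. At the Sample Size rates, 120 person-years give 12 infections in the control arm and 2.4 in the VMMC arm, so a small number of misplaced men can matter.

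**Working it through.** **Setting the rules side by side**

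1. *Enrollment.* Footnote a puts it after surgery in the VMMC arm. Randomization and Follow-Up counts the 1-week target, the 1-month reminder and the 3-month extension from enrollment, which puts it before surgery. Both cannot hold.
2. *Clock.* Taking the second meaning of enrollment does not cure the problem, because both starts of the VMMC clock still require surgery.
3. *Analysis.* Statistical Analysis estimates incidence rate ratios by Poisson regression, which needs person-time. A man without a clock start contributes none, so the analyzed set is not the randomized set.

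**Possible size of the bias**

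The article has no figure to reproduce here. The 10% in Sample Size is loss to follow-up, not non-uptake of surgery. The share *u* of VMMC men never operated on, and the ratio *k* of their HIV rate to that of operated men, are therefore assumptions.

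Suppose there is no true effect and operated men have rate *r*. The whole VMMC arm, like the control arm, then has rate (1 − u)r + u·k·r = r[1 + u(k − 1)]. Operated men against all controls give a rate ratio of 1 / [1 + u(k − 1)]:

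- u = 10%, k = 1.5: 1/1.05 = 0.95
- u = 10%, k = 2: 1/1.10 = 0.91
- u = 20%, k = 1.5: 1/1.10 = 0.91
- u = 20%, k = 2: 1/1.20 = 0.83
- any u, k = 1: 1.00, no bias
- k = 0.5: 1/0.95 = 1.05 at u = 10% and 1/0.90 = 1.11 at u = 20%, against VMMC

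The VMMC arm would fall from 120 to 108 men (u = 10%) or 96 (u = 20%).

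**What keeping every man does to the planned effect**

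Sample Size assumes 10 per 100 person-years and 80% protection. This reproduces its 2 per 100: 10 × (1 − 0.80) = 2, a rate ratio of 0.20. If unoperated men have the control rate, the intention-to-treat ratio is (1 − u) × 0.20 + u:

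- u = 10%: 0.18 + 0.10 = 0.28, a 72% effect
- u = 15%: 0.17 + 0.15 = 0.32, a 68% effect
- u = 20%: 0.16 + 0.20 = 0.36, a 64% effect

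**Time before the VMMC clock starts**

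The longest gap is 3 months plus 6 weeks, 0.25 + 6/52 = 0.365 years. At 10 per 100 person-years, 120 men would have 120 × [1 − exp(−0.10 × 0.365)] = 4.3 infections in it. With surgery at 1 week the gap is 7 weeks (7/52 = 0.135 years) and the figure is 1.6. Both are upper bounds for their waiting time, since abstinence lowers risk.

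**The case against.** The strongest reply is that no sentence removes unoperated men. Interventions promises 12 months of follow-up to all, Statistical Analysis commits to intention to treat, and Table 2 places assignment at Month 0. The wording on formal enrollment may be a loose way of describing entry to the formal follow-up phase named in the same footnote. This stands as a limit on wording. A reader might infer that such men are dropped and that intention to treat is out of reach, but the documents support only that it cannot be carried out as written. It does not close the gap, because the clock rule is separate and also requires surgery.

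A second reply is that Principal Findings explains the delayed start as giving both arms a comparable opportunity to acquire HIV. That addresses the abstinence period. It does not justify making entry depend on surgery.

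A third is that non-uptake may be small. Eligibility requires willingness to be circumcised and a foreskin covering more than half the glans, a subsidy is paid, and an assistant goes with the participant. This stands: the documents support no particular share and no direction of risk, and even 0.83 is modest beside the planned 0.20. Controls also meet a condition, the baseline questionnaire, although a much weaker one.

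A reader might also infer that men infected while waiting for surgery are screened out of the VMMC arm alone, because "HIV rapid testing will be conducted 1 month before enrollment and at enrollment" and enrollment there follows surgery. The documents do not support this. The Abstract describes the enrollment test before random assignment, Participant Recruitment and Enrollment places it in the recruitment sequence, and Table 2 shows one Month 0 HIV test and none tied to surgery. The natural reading is a test before randomization in both arms.

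**Conclusion.** The point holds as a contradiction in stated rules, not as detail left to a fuller document. Footnote a and the clock rule together give a randomized but unoperated man no enrollment and no person-time. That cannot be squared with intention to treat, with 12 months of follow-up for all men, or with the article's other use of enrollment. If the rules are applied literally, the primary HIV comparison is exposed to selection in one arm.

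The size is unknown. The null rate ratio of 0.95-0.83 rests on two assumptions that the documents do not supply: 10-20% unoperated, and 1.5-2 times the HIV rate in those men. The bias vanishes at equal risk and reverses at lower risk.

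**What to change.** - Delete the enrollment rule in footnote a, and reconcile Table 2, Interventions, Randomization and Follow-Up, and Statistical Analysis.
- Define enrollment and analysis time zero as randomization in both arms.
- Schedule the month 3, 6, 9 and 12 HIV tests for every randomized man, whether or not he was operated on, and analyze all men as assigned in the primary analysis.
- For men already randomized but not operated on, recover HIV results where they can be obtained, and report how many are missing by arm.
- Keep the post-surgery clock and the operated-only comparison as a secondary analysis.

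None of this changes the timing of surgery, the abstinence advice or the surgeon's assessment.

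The cost is a diluted effect. An assumed 15% non-uptake turns 80% into 68%, and counting the time before surgery and during abstinence dilutes it further. Any resulting loss of power should be kept apart from the separate mismatch between the 1-sided .10 in Sample Size and the 2-sided .05 in Statistical Analysis. Tracing takes some work: Results says that recruitment ran through July 2022 and data collection was expected to end by July 2023, and the article does not say whether unoperated men were tracked.
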